### Phase III: follow-up

At 24 months’ corrected age, neurodevelopment is assessed using the Parent Report of Children’s Abilities-Revised (PARCA-R) questionnaire (primary assessment tool) for all children, and (if applicable) Bayley-III/IV testing and neurological examination by trained personnel, according to national neonatal follow-up guidelines.^40^ Severe neurodevelopmental impairment is defined as a PARCA-R or Bayley cognitive or motor score <70, severe neurological dysfunction (any severe motor impairment, including cerebral palsy of at least grade 2 according to the Gross Motor Function Classification System),^41^ or severe visual or hearing impairment, as previously defined.^18^

Parental psychological assessments are repeated at 6 weeks and 24 months postpartum (figure 2, table 3).

**Table 3 T3:** Primary and secondary study parameters

Primary study parameters	
Twin level	GA at sFGR diagnosis.^5^ EFW discordance at diagnosis.^1 43^ UA Doppler abnormalities.^2^ Presence and diameter of AA anastomoses.^22 44^ Oligohydramnios (DVP<2 cm).^45^ Abnormal DV waveform (absent or reversed flow during the a-wave).^46^ Abnormal placental appearance: ultrasound asymmetry between placental shares, with increased thickness and/or heterogeneity of the smaller twin’s placental share.^44^ Major anomalies (EUROCAT criteria).^5 47^ Cord insertion site.^48^

Secondary study parameters	
I. Prenatal	**Fetal ultrasound** Standard ISUOG parameters: UA/MCA/DV PI and waveforms, MCA PSV, EFW (Hadlock 3: HC, AC, FL), amniotic fluid (DVP), bladder and stomach filling, cord insertions.^49^ Additional ultrasound measures as in tables1 2. **Fetal brain MRI** Presence of IVH, PVL, porencephalic cysts, arterial ischaemic infarction, venous infarct (PVHI), intraparenchymal haemorrhage, ventricular dilation, basal ganglia/thalamic injury, cortical injury, cerebellar injury, migration/gyration disorders, or other abnormalities. **Parental well-being** PCL-5^50^, MAAS^51^, PAAS.^52^ **Maternal** Age, pre-pregnancy BMI, smoking status, obstetric history, comorbidities, medication use, recreational drug or alcohol use, educational level (ISCED). **Gestational/fetal baseline** Gravidity, parity, mode of conception, comorbidity during pregnancy, prenatal screening/diagnostics, fetal sex and non-fatal anomalies.

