### Data analysis plan

The primary analysis will develop a multivariable logistic regression model predicting the composite outcome at diagnosis. Model performance will be evaluated by discrimination (C-statistic) and calibration (scaled Brier score), with internal validation by bootstrapping.

Secondary analyses will include:

Longitudinal modelling of ultrasound trajectories using mixed-effects models (continuous variables) and generalised estimating equations (GEE) (categorical variables), with stratification by gestational age at diagnosis (according to the most recent literature-based cut-offs) and umbilical artery Doppler flow type.Associations between antenatal imaging and placental pathology.Comparison of neurodevelopmental outcomes between co-twins using GEE or paired t-tests.Parental well-being was analysed across timepoints using mixed-effects models.Comparison of outcomes between outpatient- and inpatient-managed pregnancies.

All tests will be two-sided, with p<0.05 considered significant. Analyses will be conducted in SPSS V.25 (IBM, Chicago, USA) and/or R.

Missing data will be minimised through prospective monitoring, regular quality audits and data queries to participating centres. For the primary composite outcome, missing delivery or fetal outcome data will be actively retrieved where possible; pregnancies with unascertainable primary outcomes will be excluded from the primary prediction model analysis. For missing predictor variables, recovery from source imaging or clinical records will be attempted. If data remain missing, appropriate statistical methods will be applied based on the extent and pattern of missingness, in line with best practice for prediction modelling. Missing questionnaire data will be addressed through reminders; incomplete questionnaires will be excluded from the relevant secondary analyses, with the degree of missingness reported.

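### Incomplete questionnaires are excluded from the secondary analyses without a definition of incomplete, so partly answered scales may be lost before the planned models can use them

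*Protocol article*

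**What the plan says.** The last paragraph of the Data analysis plan gives different rules for different kinds of missing data.

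- Questionnaires: "Missing questionnaire data will be addressed through reminders", and after that "incomplete questionnaires will be excluded from the relevant secondary analyses", with the amount of missing data to be reported. The text gives no completeness threshold, scoring rule for blank items, imputation or sensitivity analysis.
- Predictors of the primary model: recovery from source records is tried first, and for what remains "appropriate statistical methods will be applied based on the extent and pattern of missingness".

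The questionnaire rule bears on two sets of secondary outcomes.

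- Parents: Phase I places assessments at inclusion and 30 weeks. Phase III adds that "Parental psychological assessments are repeated at 6 weeks and 24 months postpartum". The analysis is stated as "Parental well-being was analysed across timepoints using mixed-effects models".
- Children: Phase III names the "Parent Report of Children’s Abilities-Revised (PARCA-R) questionnaire (primary assessment tool) for all children", with Bayley testing and neurological examination only where applicable under national guidelines. The analysis is "Comparison of neurodevelopmental outcomes between co-twins using GEE or paired t-tests".

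**The concern.** This is a stated analysis decision, not a detail left open for a later document. An SAP that kept partly answered scales would depart from the published text if incomplete is taken literally.

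The rule also sits poorly with the rest of the plan. Mixed-effects models and GEE can work with unbalanced data, but the rule removes observed answers before either model is fitted. For predictors, the same paragraph promises handling suited to how much is missing and in what pattern. Questionnaires get deletion whatever the amount or pattern, and no reason is given for the difference.

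Two things are at stake. The first is precision in the analyses of parental well-being, attachment and 24-month neurodevelopment. The second is selection. If distressed or bereaved parents, or parents of an impaired child, leave items blank more often, the complete responders are not representative of the cohort.

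**Working it through.** **The plan's own figure.** The article gives no power, sample size or missingness rate for any questionnaire analysis. Its one sample-size figure, 274 pairs, belongs to the primary model. The precision step of the cited four-step approach, with the stated 23% incidence and an assumed margin of 0.05, gives (1.96/0.05)² × 0.23 × 0.77 = 272.1, rounded up to 273, which is close to 274. Nothing below changes that figure.

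**Share of questionnaires lost.** Assumptions: k items, each blank with probability q, independently, and one blank item makes the form incomplete. The share lost is 1 − (1 − q)^k. For k = 20:

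| q per item | calculation | share lost |
|---|---|---|
| 0.5% | 1 − 0.995^20 = 1 − 0.905 | about 10% |
| 1% | 1 − 0.99^20 = 1 − 0.818 | 18% |
| 2% | 1 − 0.98^20 = 1 − 0.668 | 33% |

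Scale length matters. At q = 1% the loss is 10% for 10 items (1 − 0.904) and 26% for 30 items (1 − 0.740). Independence is unfavourable to the plan: for the same per-item rate, clustering of blanks within respondents leaves fewer forms affected.

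**Effect on power.** Assumption: a comparison with 80% power at two-sided 0.05 if every returned form is used. With share L excluded, power = Φ((1.960 + 0.842) × √(1 − L) − 1.960). In a paired t-test one excluded form removes the pair, so with independent exclusions in the two twins √(1 − L) becomes (1 − L).

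| L | per-questionnaire loss | paired t-test, independent exclusions |
|---|---|---|
| 5% | 78% | 76% |
| 10% | 76% | 71% |
| 20% | 71% | 61% |
| 30% | 65% | 50% |

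If exclusions always hit both twins together, for example because the same parent answers for both, the paired test follows the middle column.

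**Effect on a mean.** Shift = L × (difference between excluded and retained respondents). For an assumed difference of 0.2 to 0.5 SD, the shift is 0.02 to 0.05 SD at L = 10% and 0.04 to 0.10 SD at L = 20%. With no difference there is no shift.

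**Where the loss falls.**

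- Mixed-effects model for parents: the excluded wave is lost and the parent's other waves stay.
- GEE for children: the excluded twin is lost and the co-twin stays.
- Paired t-test for children: the pair is lost.
- Severe impairment: Phase III also allows classification by Bayley score, severe neurological dysfunction, or severe visual or hearing impairment, so some children without a usable PARCA-R can still be classified.

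**The case against.** The strongest reply is that the article never says one blank item makes a form incomplete. The instruments are described as validated, and incomplete could mean not scorable under the instrument's own rules. A condensed article may leave such thresholds to the full protocol or SAP. This stands in part: the one-blank-item reading is the literal one, but it is not established. The remedy on that reading is still to say so in the text.

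A reader might multiply across the four assessment times and infer that, at 1% missing per item, only 0.818⁴ = 0.448, or about 45%, of parents would remain. The documents do not support this. The rule excludes questionnaires, not parents, and the planned mixed model does not need all waves. Table 3 lists only the PCL-5 in all three phases; the attachment scales differ before birth (MAAS, PAAS) and after it (MPAS, PPAS).

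A reader might also infer that the results will be biased towards better-off families, or that every child with an incomplete PARCA-R drops out. The first is plausible, but nothing in the article shows it. The second ignores the other routes to classification and the co-twin kept by GEE.

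Reminders, monitoring, audits, data queries and reporting of missingness reduce or disclose the problem. They do not recover a partly answered scale. It is also fair to say that the item count, the missing rates and independence are all assumed.

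**Conclusion.** The point holds in limited form. The article fixes an exclusion rule for incomplete questionnaires, does not define the term, and applies a weaker standard than it sets for predictors. Taken literally, the rule discards usable answers and limits the secondary analyses to complete responders.

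Its size cannot be derived from the document. The losses of about 10%, 18% and 33% rest on an assumed 20-item scale and independent blanks at 0.5%, 1% and 2% per item. The power figures rest on an assumed 80% baseline. Bias requires incompleteness to depend on the outcome, which remains a possibility only. The paired t-test is the most exposed analysis; the mixed model and GEE lose single questionnaires.

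Only secondary outcomes are touched. The primary model and its 274 pairs are not, so the priority is minor to moderate.

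**What to change.** Replace the exclusion rule with wording such as:

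> Partly completed questionnaires will be scored by the instrument's published missing-item rule where one exists; otherwise, missing items will be multiply imputed using the other items, other waves where available, and pregnancy outcome. The resulting scores enter the planned mixed-effects models (parents) and GEE (children, keeping a twin whose co-twin lacks a score). The complete-questionnaire analysis is a sensitivity analysis, and complete and incomplete responders are compared on baseline characteristics.

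If the intended meaning was already not scorable under the instrument's rules, state that for each instrument, and add the sensitivity analysis and the comparison of responders.

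The change needs no new data. It costs modest extra analysis work and brings a missing-at-random assumption, against which the complete-questionnaire analysis serves as a check. Recruitment runs to the end of 2026, so the wording can be settled before the final analyses.

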### Trial status

Study preparation began in 2022. Recruitment started in March 2023 and was expanded to all centres in June 2024. By December 2025, 209 twin pairs had been enrolled (76% of the target), with approximately 10 new pairs recruited per month. Recruitment will continue until the end of 2026.

### Patient and public involvement

Patients and members of the public were not involved in the scientific design, methodology or conduct of the CONTRAST study. However, a mother who previously gave birth to twins affected by sFGR contributed to the development and refinement of the patient counselling summary flyer used during recruitment. In addition, representatives from the TAPS Support Foundation provided feedback on the wording of participant questionnaires and on communication materials to ensure clarity and accessibility. They also interviewed members of the study team and disseminated information about the study in lay terms on their public website. On completion of the study, a plain-language summary of the results will be made available on the clinical trial registration website and shared through our institutional communication channels for participants and the wider public.

### Ethics and dissemination

The CONTRAST study protocol and informed consent procedures have been approved by the by the institutional review boards or ethical review authority of all participating centres: Leiden University Medical Center (NL81805.058.22), University Hospitals Leuven (S67514), Karolinska University Hospital (2023-04704-01), BCNatal (HCB/2023/0123), Mount Sinai (23-0161-E) and Boston Children’s Hospital (IRB-P00046170). Written informed consent is obtained from all participants prior to inclusion.

Data are managed according to Good Clinical Practice and the General Data Protection Regulation. All information is coded and stored in a secure, web-based electronic case report form (CASTOR). Identifiable information is stored separately and accessible only to local principal investigators. Access to coded data is restricted to study investigators and authorised monitors or supervisory authorities. Data will be stored for at least 15 years after study completion.

Ultrasound images and cardiac clips are pseudonymised and uploaded to CASTOR, with central analysis performed at Leiden University Medical Center. Only coded data are used in analyses, reports and publications.

Findings from this study will be disseminated through presentations at national and international scientific conferences and publications in peer-reviewed journals, in line with the CCMO statement on publication policy. A plain-language summary of the study results will also be published on the clinical trial registration website for participants and the general public. Where appropriate, data may be made available for secondary analyses to address the study objectives, subject to ethical and legal requirements.
